# The calculation of fluid retention: intravenous fluids + enteral nutrition − (urine output + drainage volume).

### Outcomes

Table 1 shows the collected procedures, data, and outcomes.

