To ensure pharmacological consistency across centers, the study medication is standardized. Vitamin C is sourced from a single manufacturer (Chengdu Brilliant Pharmaceutical Co., Ltd., Chengdu, China; National Medicine Permission Number: H32022732) from one production batch. The medication is supplied in ampoules of 1 g per 5 mL (200 mg/mL). The solvent is water for injection, with sodium metabisulfite, cysteine hydrochloride, disodium edetate, and anhydrous sodium carbonate as excipients. To avoid fluid overload in SAP patients, vitamin C is given as the undiluted original solution. For the intervention group, the weight-based dose (500 mg/kg/day) is drawn into 50 mL light-proof syringes by an unblinded drug preparation nurse (UDPN). The solution is administered continuously via a central venous catheter using a micro-infusion pump at 2 g/h. The control group receives 0.9% normal saline at 10 mL/h to match the vitamin C infusion, for a daily sodium chloride load of approximately 2.16 g. Throughout the intervention period, patients will be closely monitored for adverse effects. If complications such as cystinuria, gout, hyperoxaluria, oxalate deposition, or urate kidney stones occur, the dosage should be adjusted as clinically indicated. In severe cases, the trial may be discontinued.

During the intervention, if an interruption occurs (such as CT transport, infusion pump disconnection, central line failure) the infusion will be temporarily paused and later resumed at the identical constant rate of 2 g/h. Catch-up boluses or rate increases are prohibited. Interruptions under 2 h per 24-h cycle are considered acceptable. Longer interruptions are documented as protocol deviations but the patient remains in the study under ITT analysis.

Vitamin C has low molecular weight and high water solubility, so it is cleared during CRRT. The baseline dose is high enough that plasma levels should stay well above the therapeutic threshold even during continuous renal replacement therapy (CRRT). Keeping the dose unchanged avoids rebound toxicity risk if CRRT is interrupted unexpectedly, and it keeps the protocol consistent across all study centers. We will document CRRT parameters (duration, modality, effluent dose) in Table 1 and include them in statistical adjustments and subgroup analyses to capture how CRRT affects drug exposure.

**Table 1 tab1:** Collected procedures, data, and outcomes.

Procedures	Day 0	Day 1	Day 3	Day 7	Day 14	Day 28	Day 180

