Eligible criteria	x						
Informed consent	x						
Demographic and medical data	x						
Vital signs	x	x	x	x	x	x	
Laboratory biomarkers^*^	x	x	x	x	x	x	
Plasma vitamin C concentration	x	x	x	x			
SOFA score	x	x	x	x	x	x	
APACHE II score	x	x	x	x	x	x	
Antibiotics							
Surgical intervention							
Continuous renal replacement therapy (modalities, durations, and intensities)	x	x	x	x	x	x	
Mechanical ventilation	x	x	x	x	x	x	
Vasoactive drugs	x	x	x	x	x	x	
Gut microbiota	x	x	x	x	x	x	
Fluid retention^#^							
Abdominal CT scan	x			x	x	x	
Death							x
Hospital stay							x

CT, computed tomography; SOFA, sequential organ failure assessment; APACHE II, acute physiology and chronic health evaluation II.

* Laboratory biomarkers include: blood cell analysis, blood gas analysis, C-reactive protein, procalcitonin, coagulation test, liver function, renal function, NT-proBNP, TnI, cytokines, immunoglobulin, pancreatic enzymes.

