### Primary outcome

This study assesses the effect of HDIVC on organ support-free days (OSFD) within the first 14 days in SAP patients. OSFD refers to the number of days a patient does not require circulatory support (vasoactive agents), respiratory support (mechanical ventilation), or renal support (renal replacement therapy). For patients who die within the 14-day observation period, OSFD is assigned a value of 0 day.

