### Secondary outcome

The secondary outcomes are: (1) ICU all-cause mortality, defined as death from any cause from randomization to ICU discharge or transfer. (2) Early SAP inflammatory markers, including C-reactive protein and cytokines IL-6, IL-1, and IL-10. (3) Organ function scores, including SOFA and modified Marshall scores. (4) Fluid retention. (5) Disease severity scores, including APACHE II and BISAP scores. (6) Pancreatic necrosis measured by CTSI scores. (7) Other prognostic indicators including the incidence of infected pancreatic necrosis, ICU length of stay, and hospitalization costs. (8) Plasma vitamin C concentrations before and after treatment. (9) Adverse events related to vitamin C. (10) Gut microbiota composition.

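### The fluid-retention formula has no term for fluid removed by renal replacement therapy, so it overstates this secondary outcome in patients on CRRT by their net removal

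*Protocol article*

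**What the plan says.** The protocol article lists fluid retention among its secondary outcomes ("4) Fluid retention", Secondary outcome). The footnote to Table 1 gives the formula: "intravenous fluids + enteral nutrition − (urine output + drainage volume". It has two intake terms and two output terms, the latter being "urine output + drainage volume". The article does not define drainage volume.

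CRRT appears in three other places:
- **Primary outcome:** one of the three kinds of support counted in organ support-free days (OSFD) is "renal support (renal replacement therapy".
- **Table 1:** CRRT has its own row, "Continuous renal replacement therapy (modalities, durations, and intensities".
- **Intervention:** "We will document CRRT parameters (duration, modality, effluent dose) in Table 1". These parameters are to enter adjustments and "subgroup analyses to capture how CRRT affects drug exposure".

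None of these places names net fluid removal as a recorded item or brings it into the balance.

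**The concern.** A balance that omits one route of output is wrong for every patient who uses that route. Here those patients are not rare exceptions by the trial's own account. Eligibility requires persistent organ failure, renal support is part of the primary outcome, and the article gives a paragraph to vitamin C dosing during CRRT. In a patient with little urine who is on CRRT, the machine may be the main way fluid leaves. The formula would then record the intake and very little output.

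The error need not cancel between arms. CRRT starts after randomization, and treatment could move its use either way: the article expects HDIVC to improve organ function, and it also monitors acute kidney injury and oxalate nephropathy as possible harms. If CRRT use differs by arm, part of any difference in fluid retention would come from the formula.

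**Working it through.** **The plan's own figures.** The article states no expected value, SD or effect size for fluid retention, so there is nothing to reproduce for this outcome. Its sample-size calculation concerns OSFD only: 2 × (5 × (1.96 + 0.84) / 2)² ≈ 98 per group; 98 × 1.15 = 112.7, so 113; 113 / 0.95 = 118.9, so 119 per group and 238 in total. Nothing in that chain uses the fluid formula.

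**Size of the error for one patient.** Let IV be intravenous fluids, EN enteral nutrition, U urine, D drainage, and F net fluid removed by renal replacement therapy.

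- Printed: R = IV + EN − (U + D)
- With machine removal counted: R* = IV + EN − (U + D + F)
- Difference: R − R* = F

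The overstatement is exactly F, and it is zero when F is zero.

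**In litres, under assumed rates.** The article gives no rate. Take continuous running for 24 hours:

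| Assumed net removal (mL/h) | Overstatement per CRRT day (L) |
|---|---|
| 0 | 0 |
| 25 | 0.6 |
| 50 | 1.2 |
| 100 | 2.4 |
| 125 | 3.0 |

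One litre per day is reached at 1000 / 24 ≈ 42 mL/h.

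**One illustrative CRRT day (all volumes assumed).** IV 3.0 L, EN 0.5 L, urine 0.1 L, drainage 0.4 L. The printed formula gives 3.0 + 0.5 − (0.1 + 0.4) = +3.0 L whatever the machine removes. With removal counted, the balance is +1.8 L at 50 mL/h, +0.6 L at 100 mL/h and 0 L at 125 mL/h.

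**Between arms.** If net removal per CRRT day is the same in both arms, the artificial difference is (difference in CRRT use) × F.

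- Assumed 10-percentage-point difference in the share of patients on CRRT on a given day: 0.10 × (0 to 3.0 L) = 0 to 0.30 L in that day's mean.
- If a total over the period were analysed, with an assumed difference of 0.5 mean CRRT days: 0.5 × (0 to 3.0 L) = 0 to 1.5 L.

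The arm with more machine removal looks worse. The documents do not say which arm that would be.

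**Can the recorded CRRT data repair it?** No. Duration and modality are not volumes. Effluent also contains dialysate or replacement fluid, so effluent dose or intensity does not isolate net removal. Adjusting for CRRT conditions on a variable that arises after randomization, and it cannot restore a volume that was not recorded. The article also gives the purpose of that adjustment as drug exposure, not fluid balance.

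**The case against.** The strongest reply is that little depends on this outcome. Fluid retention is not one of the four outcomes named in the fixed testing sequence under Statistical methods. At best it falls among the remaining ones, reached only if ICU mortality, SOFA, CRP and APACHE II are all significant. This stands, and it limits the weight of the point.

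A second reply is that the size rests wholly on assumption. The article gives no removal rate, no expected share of patients on CRRT and no expected difference between arms. This also stands. The litres above are a range that starts at zero.

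A third reply is that a condensed article may use drainage volume loosely, and a fuller manual may count ultrafiltrate within it. This is weak. The formula is printed as a complete definition and CRRT is listed separately in the same table. If ultrafiltrate is meant to be included, the footnote should say so, or eight centers may calculate the outcome differently.

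A reader might also infer more than the documents support:
- **That the formula has the wrong sign, so more machine removal scores as more retention.** It does not. With intake, urine and drainage fixed, the score does not move. Machine removal gets zero weight, not negative weight.
- **That the error accumulates day by day.** The article does not say whether the outcome is analysed daily or as a running total.
- **That the primary outcome is compromised because renal support is one of its components.** OSFD counts days without support and never uses this formula.
- **That the trial's rationale is undermined.** The fluid-balance signal in the earlier trial came from moderately severe disease, which is not enrolled here, and the dose rationale under Intervention refers to inflammatory biomarkers.

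**Conclusion.** The definition is incomplete as printed. It overstates fluid retention in any patient with net fluid removal by renal replacement therapy, by exactly that removal. This algebra needs no assumption beyond reading drainage volume as not including ultrafiltrate. The size does need one: at 0 to 125 mL/h over 24 hours it is 0 to 3.0 L per CRRT day, and it is nil where CRRT runs without net removal.

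A spurious difference between arms also requires net machine removal to differ by arm. That is possible, but the documents do not establish it. The consequence is confined to one secondary outcome outside the four named steps of the hierarchy. It should be corrected, but it does not touch the trial's main conclusion or its sample size.

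**What to change.** Add net fluid removed by CRRT or dialysis to the output terms in the Table 1 footnote, so that outputs are urine, drainage and net removal. State that drainage volume excludes ultrafiltrate, so that nothing is counted twice. Record net removal in the eCRF for each balance period, beside the CRRT items already collected. This changes a measurement definition only, not any treatment.

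The cost is one line of text and one data field that is normally on the ICU fluid chart. The 34 patients reported as recruited at the lead center, and any enrolled since, need the volume retrieved from charts. The article says source documents are kept, so this should be feasible, and the work grows with each further enrollment. Other unlisted intake or losses could be reviewed at the same time, but the point made here does not depend on them.

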### Primary outcome

This study assesses the effect of HDIVC on organ support-free days (OSFD) within the first 14 days in SAP patients. OSFD refers to the number of days a patient does not require circulatory support (vasoactive agents), respiratory support (mechanical ventilation), or renal support (renal replacement therapy). For patients who die within the 14-day observation period, OSFD is assigned a value of 0 day.

### Secondary outcome

The secondary outcomes are: (1) ICU all-cause mortality, defined as death from any cause from randomization to ICU discharge or transfer. (2) Early SAP inflammatory markers, including C-reactive protein and cytokines IL-6, IL-1, and IL-10. (3) Organ function scores, including SOFA and modified Marshall scores. (4) Fluid retention. (5) Disease severity scores, including APACHE II and BISAP scores. (6) Pancreatic necrosis measured by CTSI scores. (7) Other prognostic indicators including the incidence of infected pancreatic necrosis, ICU length of stay, and hospitalization costs. (8) Plasma vitamin C concentrations before and after treatment. (9) Adverse events related to vitamin C. (10) Gut microbiota composition.

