## Introduction

Severe acute pancreatitis (SAP) is the most life-threatening form of acute pancreatitis (AP), and its incidence is rising globally (1). In Western countries, annual incidence runs from 13 to 45 per 100,000. In China, rates climbed from 0.19 to 0.71% over the past two decades. Mortality still sits between 13 and 35% despite better management (2).

Antioxidant therapy is important in SAP management. During early disease, oxidative stress from infection and uncontrolled reactive oxygen species (ROS) release triggers systemic inflammatory response syndrome (SIRS), which can progress to multiple organ dysfunction syndrome (MODS) (3). Therefore, timely elimination of excessive ROS is considered as a critical therapeutic target for improving clinical outcomes.

Vitamin C, a potent plasma antioxidant, effectively neutralizes ROS (3). Preclinical and clinical studies have demonstrated its anti-inflammatory properties and endothelial protective effects (4–6). Although oral administration is common (7), it fails to achieve therapeutic plasma concentrations in critically ill patients. Because critical illness drives rapid ROS overproduction and impairs gut absorption, oral dosing raises plasma levels to only around 150 μmol/L, well below what is needed to affect oxidative stress (8). Recently, high-dose intravenous vitamin C (HDIVC) has emerged as a promising intervention in critical care therapy. Growing evidence supports its potential efficacy in SAP, acute respiratory distress syndrome (ARDS), and severe coronavirus disease 2019 (COVID-19) (9).

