In our preclinical work, vitamin C supplementation lowered inflammatory markers, mortality, and pancreatic necrosis in SAP mice (15, 16). Whether this carries over to humans is unclear. Existing clinical data are inconsistent and come from small samples, insufficient dosing, or cohorts weighted toward mild disease (17). From September 2019 to December 2023, we conducted a single-center, double-blind, randomized, placebo-controlled trial (ChiCTR1900022022) investigating HDIVC (200 mg/kg/24 h, 1 g/h, for 7 days) (6). The primary outcome of 28-day mortality did not differ significantly between treatment groups in the overall cohort (*n* = 212). However, prespecified subgroup analysis revealed that MSAP patients receiving HDIVC demonstrated significant reductions in C-reactive protein levels and improved fluid balance. These findings suggest HDIVC may attenuate inflammatory responses in MSAP, though its therapeutic value in SAP requires confirmation through adequately powered multicenter randomized controlled trials. Extensive preclinical investigations over the past few decades have established the therapeutic potential of HDIVC in SAP, with mechanistic understanding progressively refined through cellular, animal, and early-phase human studies. While these foundational studies show biological plausibility, current clinical evidence remains limited to underpowered single-center trials, precluding definitive conclusions about therapeutic efficacy. To address this critical evidence gap, we propose a multicenter, prospective, randomized, double-blind, placebo-controlled trial evaluating early HDIVC administration (500 mg/kg/day for 7 days, 2 g/h) in SAP patients. The primary outcome is organ support-free days (OSFD) within the first 14 days. Secondary outcomes include ICU all-cause mortality, inflammatory biomarker, organ failure scores and fluid retention. This study aims to determine whether HDIVC represents a clinically meaningful, cost-effective therapeutic intervention capable of improving outcomes in this high-mortality condition, with potential to inform future guideline recommendations.

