### Statistical methods

The statistical analysis will follow an intention-to-treat (ITT), per-protocol (PP), and safety population approach. All statistical tests will be two-sided, with a *p*-value < 0.05 considered statistically significant. Baseline characteristics will be summarized using descriptive statistics. For quantitative variables, descriptive statistics will include calculations of mean, standard deviation, median, minimum, maximum, and interquartile range (IQR). For categorical variables, descriptive statistics will report frequencies and percentages for each category.

The primary outcome, OSFD within the first 14 days, will be analyzed using a linear mixed-effects model with center included as a random intercept, allowing quantification and adjustment for between-center variability. Sensitivity analyses will treat center as a fixed effect or omit center effects to assess robustness. A treatment-by-center interaction test will be performed to evaluate heterogeneity of treatment effect across sites. The intraclass correlation coefficient (ICC) from the null model will be reported. To control the familywise type I error rate for secondary outcomes, a hierarchical (fixed-sequence) testing procedure is applied. The pre-specified order is: (1) ICU all-cause mortality, (2) SOFA score at Day 7, (3) C-reactive protein at Day 7, (4) APACHE II score at Day 7, followed by all remaining secondary outcomes. Each outcome is formally tested only if all preceding outcomes in the hierarchy reach statistical significance at the two-sided *α* = 0.05 level. Outcomes below the hierarchical chain—including cytokine levels (IL-6, IL-1, IL-10), BISAP score, CTSI score, ICU length of stay, hospitalization costs, and gut microbiota composition—are designated as exploratory. Their *p*-values will be reported descriptively without formal inferential claims.

Bioinformatics processing will use QIIME2 with DADA2 denoising to generate amplicon sequence variants (ASVs), and taxonomic assignment will be performed against the SILVA database. Alpha diversity (Shannon, Chao1 indices) will be compared between groups using Wilcoxon rank-sum tests. Beta diversity (Bray-Curtis, UniFrac distances) will be visualized by principal coordinate analysis (PCoA) and tested by PERMANOVA. Differential abundance analysis will be conducted using LEfSe (LDA > 2.0) and MaAsLin2. Longitudinal changes will be analyzed using linear mixed-effects models if serial samples are available.

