### Expected results

We anticipate that the continuous administration of HDIVC at 500 mg/kg/day for 7 days will result in an improvement in the primary outcome of OSFD within the first 14 days among SAP patients compared to the placebo group. HDIVC is expected to effectively neutralize excessive ROS and halt the progression of MODS. We also expect that HDIVC will lead to improvements in ICU all-cause mortality, early SAP inflammatory markers, organ function scores, fluid retention, disease severity scores, pancreatic necrosis, ICU length of stay, and hospitalization costs.

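### Raw ICU length of stay and hospitalization costs take no account of death, so the arm with more deaths can look better on both, and they cannot support the cost-effectiveness aim (minor)

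*Protocol article*

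**What the plan says.** All references are to the protocol article.

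- **Secondary outcome**, item (7), names the measures: "Other prognostic indicators including the incidence of infected pancreatic necrosis, ICU length of stay, and hospitalization costs". It gives no rule for patients who die.
- **Primary outcome** does give one: "For patients who die within the 14-day observation period, OSFD is assigned a value of 0 day".
- **Expected results** lists, among the improvements anticipated with HDIVC, "pancreatic necrosis, ICU length of stay, and hospitalization costs".
- **Introduction** gives the disease context, "Mortality still sits between 13 and 35% despite better management", and the aim: "This study aims to determine whether HDIVC represents a clinically meaningful, cost-effective therapeutic intervention". Hospitalization cost is the only economic measure among the outcomes.
- **Statistical methods** limits the weight of both measures: "ICU length of stay, hospitalization costs, and gut microbiota composition—are designated as exploratory". Their p-values are to be descriptive. ICU all-cause mortality stands first in the fixed testing sequence.

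**The concern.** Death ends an ICU stay and stops hospital costs from accruing. A patient who dies on Day 4 therefore contributes a shorter stay than a survivor discharged from the ICU on Day 20, although the outcome is worse. The missing-data provisions (multiple imputation, otherwise last observation carried forward) do not help, because the stay and cost of a patient who died are fully observed.

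The distortion can run either way. If HDIVC were harmful, stay and cost could look better on it. If it saved lives, they could look worse. The Discussion itself cites a sepsis trial in which vitamin C raised the risk of death or persistent organ dysfunction (RR 1.21, 95% CI 1.04–1.40), so unequal mortality in the unfavourable direction is a reasonable case to plan for. At stake is how two descriptive comparisons are read, and whether a stated aim can be met. The primary inference is not at stake.

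**Working it through.** **The plan's own figure.** The article states no figure for stay or costs. Its only calculation is the sample size for organ support-free days: 2 × [5 × (1.960 + 0.842) / 2]² = 98.1 (stated as 98); 98 × 1.15 = 112.7, so 113; 113 / 0.95 = 118.9, so 119 per group and 238 in all. It reproduces, apart from 98.1 being rounded down. A death rule for item (7) does not change it. The 119 per arm is used below.

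**Inputs.**
- Mortality of 13% to 35%: Introduction.
- Mean ICU stay of survivors (S) and of patients who die (D): not in the document, so assumed and varied.
- Survivors' stay is taken as identical in both arms, so any difference comes from deaths alone.

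**Formula.** With mortality p, an arm's mean stay is (1 − p) × S + p × D. The difference between arms (T minus C) is (p_T − p_C) × (D − S).

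**Main illustration: S = 20, mortality 25% v 35%.**

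| D (days) | Mean stay at 25% | Mean stay at 35% | Difference |
|---|---|---|---|
| 5 | 16.25 | 14.75 | −1.5 |
| 10 | 17.5 | 16.5 | −1.0 |
| 15 | 18.75 | 18.25 | −0.5 |
| 20 | 20.0 | 20.0 | 0 |
| 25 | 21.25 | 21.75 | +0.5 |

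**Other assumed stays.** For (S, D) = (20, 6), (20, 10), (15, 7) and (25, 7), with 5 to 10 points more deaths, mean stay falls by 0.4 to 1.8 days, about 3% to 10%. With the two ends of the stated mortality range set against each other (13% v 35%), the fall is 1.8 to 4.0 days.

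**How often a trial of this size would show it.** In 3,000 simulated trials with 119 per arm, gamma-distributed stays, S = 20, D = 7 and a rank-sum test:

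| Mortality, control v HDIVC | Nominally significant shorter stay on HDIVC, no death rule |
|---|---|
| 25% v 25% | 2.6% |
| 25% v 30% | 8% |
| 25% v 35% | 20% |
| 13% v 35% | 67% |

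At 25% v 35%, the arm with more deaths has the shorter mean stay in 83% of trials. With death ranked worst, the false benefit falls to about 0% and harm is flagged in about 27%. With D = S = 20 and no death rule, the false-benefit rate at 25% v 35% is 2.8%, about what chance gives.

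**Does the replacement point the right way?** Take S = 20 and suppose that all survivors leave the ICU, and all deaths occur, by Day 28. Survivors then average 28 − 20 = 8 ICU-free days and patients who die score 0. The arm means are 0.75 × 8 = 6.0 and 0.65 × 8 = 5.2. The arm with more deaths is now worse by 0.8 days, whatever D is.

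**Costs.** The document gives no cost figures. The argument carries over only as far as costs rise with days in hospital, which is an assumption.

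**The case against.** The strongest reply is that the plan already limits the damage. Stay and costs are exploratory, their p-values are descriptive, and ICU mortality is tested first, so an excess of deaths would be reported in the same paper. The Statistical methods section also places all remaining secondary outcomes at the end of the formal sequence, which sits awkwardly with calling these same ones exploratory. On that reading too, they are reached only after mortality is significant. At observed rates of 25% v 35% with 119 per arm, z = 0.10 / √(0.30 × 0.70 × 2/119) = 1.68, p ≈ 0.09, and the sequence stops. A reader might infer that the plan opens a route to a formal false claim of benefit or of cost-effectiveness. It does not.

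Three other strong readings also fail.
- A reader might infer that the plan defines lower stay and cost as better. It does not say so. The direction is inferred from the anticipated improvements, though it is hard to read them otherwise.
- A reader might infer that deaths always flatter the arm that has more of them. That needs both unequal mortality and shorter stays among those who die.
- A reader might extend the point to infected pancreatic necrosis. A simple proportion over fixed follow-up already equals the cumulative incidence with death competing, so little is gained there.

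It can also be said that a condensed article may leave death handling to the full protocol or analysis plan. That would answer a complaint about missing detail. Here, however, the article itself chooses raw length of stay as the measure, while writing death into the definition of the primary outcome.

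Reporting mortality alongside is only partial protection. Power to detect 25% v 35% with 119 per arm is about 39% (normal approximation, two-sided 0.05). A shorter stay and lower cost could well stand next to a mortality difference described as not significant.

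**Conclusion.** The point holds as a minor one. Raw ICU stay and hospitalization costs do not account for death, and improvements in both are anticipated. With survivors' stay assumed at 20 days and decedents' at 5 to 15, a 10-point mortality excess shortens mean stay by 0.5 to 1.5 days with no benefit to anyone. This rests on the assumed stays and on unequal mortality; it is nil at equal stays and reverses if those who die stay longer. No formal claim, primary result or sample size is affected.

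Two things remain. The descriptive comparison can mislead. And an exploratory cost comparison without inferential claims, with no cost-effectiveness analysis described, cannot deliver an aim of determining whether HDIVC is cost-effective. The Abstract's use of the term is milder: it is conditional on proven efficacy and tied to survival.

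**What to change.** 1. In Secondary outcome (7), replace raw ICU length of stay with ICU-free days to Day 28, giving patients who die by Day 28 the worst value. An alternative is the cumulative incidence of ICU discharge alive, with death as a competing event. Raw stay in survivors can be kept as description.
2. Present the difference in hospitalization costs beside the difference in ICU all-cause mortality, already secondary outcome (1), and draw no conclusion from costs alone.
3. Remove the cost-effectiveness wording from the aim in the Introduction.

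The cost is wording only. ICU discharge and vital status are already needed for secondary outcomes (1) and (7), and follow-up runs to 180 days or death. The one drawback is that ICU-free days is less intuitive than length of stay. The change should be made before unblinding, because a switch of measure afterwards would be hard to defend.
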